## Abstract

**Background:**

Atlantoaxial rotatory subluxation (AARS) is a common cause of acquired painful torticollis in children. Conservative treatment is widely used, but high-quality randomized evidence for structured muscle-focused rehabilitation is limited. Musculoskeletal ultrasound, especially shear-wave elastography (SWE), can measure cervical muscle stiffness in a non-invasive way. This trial aims to test the efficacy and safety of joint mobilization combined with cervical resistance training in children with AARS. It will also examine whether ultrasound-based measures can detect treatment-related changes in cervical muscle stiffness.

**Methods:**

This is a single-center, assessor- and analyst-blinded, randomized controlled superiority trial with two parallel groups. Seventy children aged 2–18 years with clinically and radiologically confirmed AARS will be randomly assigned in a 1:1 ratio to joint mobilization plus cervical resistance training or joint mobilization alone. Both groups will receive treatment 3 times per week for 4 weeks. The primary outcome is affected-side sternocleidomastoid stiffness at week 4 measured by SWE and adjusted for baseline stiffness. Secondary outcomes include bilateral sternocleidomastoid and upper trapezius SWE parameters, pain intensity, cervical disability, cervical rotation range of motion, overall clinical efficacy, and recurrence-related outcomes. SWE outcomes will be assessed at baseline, week 2, and week 4. Pain and disability outcomes will be assessed at baseline, week 2, week 4, and at 3 and 6 months after treatment. Cervical rotation range of motion will be assessed at baseline, week 2, and week 4. Recurrence-related outcomes will be recorded at the 3- and 6-month follow-up visits.

**Discussion:**

This randomized controlled trial is designed to provide high-quality evidence regarding the effectiveness of joint mobilization combined with cervical resistance training for pediatric AARS. By incorporating musculoskeletal ultrasound as an objective assessment tool, the study aims to elucidate the relationship between cervical muscle mechanical properties and clinical outcomes. The findings may contribute to the development of standardized, muscle-focused conservative treatment strategies for children with AARS.

**Trial registration:**

International Traditional Medicine Clinical Trial Registry (ITMCTR2025002448), registered on 27 October 2025.

## Introduction

Atlantoaxial rotatory subluxation (AARS) is a cervical disorder in which the atlas (C1) rotates abnormally or becomes fixed relative to the axis (C2). The condition often causes painful torticollis, abnormal head posture and restricted neck movement [1–3]. A characteristic physical sign is the so-called “cock-robin” posture, in which the head is tilted to one side with the chin rotated towards the opposite side [4]. Epidemiological studies indicate that atlantoaxial disorders are proportionally more common in pediatric populations than in adults, with AARS representing one of the most frequent cervical spine conditions in children, particularly those under 12 years of age [5]. It may develop after infection, inflammation, trauma, or otolaryngological procedures. Grisel’s syndrome refers to a non-traumatic form of AARS that occurs secondary to upper airway infection, inflammation, or recent head and neck surgery, especially otolaryngological procedures [2,6]. Delayed recognition may increase treatment difficulty and may lead to more invasive management [3,7,8].

The atlantoaxial joint is the most mobile part of the cervical spine and contributes about 60% of total cervical rotation [9]. Children are more prone to AARS because of developmental features such as greater ligamentous laxity, immature bony anatomy, shallow articular surfaces, and relatively limited upper cervical stability [10]. In many children, mild trauma, upper respiratory infection, or local inflammation can disturb atlantoaxial mechanics and lead to rotational fixation rather than a complete dislocation [3,11]. Abnormal atlantoaxial alignment may disturb cervical biomechanics and induce pain, muscle guarding, and compensatory posturing. As cervical stability depends on the integrated function of joints, ligaments, and muscles, joint dysfunction may also impair deep cervical muscle control and promote compensatory overactivity of superficial muscles such as the sternocleidomastoid and trapezius [7,12]. This mechanical change may increase pain, muscle guarding, and local soft-tissue stress. It may also disturb normal movement control around the neck.

Conservative treatment is the main approach for most non-surgical cases of pediatric AARS [1,3,8]. Common options include rest, analgesia, cervical collar immobilization, traction, and manual therapy. Many children improve with these measures, but treatment response is not always stable, and some children continue to show pain, limited motion, or recurrent symptoms [11–14]. Because of this, clinicians still need rehabilitation programs that can better restore muscle control and cervical stability after joint alignment improves.

Joint mobilization is often used in conservative care for cervical dysfunction and neck pain [15–17]. This method may reduce pain, improve segmental mobility, ease protective muscle guarding, and help restore more normal movement. Cervical resistance training may improve muscle activation, endurance, and motor control. These effects may support recovery after joint malalignment is corrected or reduced. However, most evidence for mobilization and exercise comes from other cervical disorders or adult populations rather than pediatric AARS [15,18,19]. This supports the need for a pediatric randomized trial.

Musculoskeletal ultrasound is being used more often in pediatric rehabilitation because it is safe, non-invasive, radiation-free, and suitable for repeated bedside assessment [20,21]. In cervical disorders, ultrasound can show muscle size, symmetry, and soft-tissue status. Shear-wave elastography can also quantify muscle stiffness and provide a more objective view of tissue change. These features make ultrasound a useful tool for tracking recovery and studying treatment effects in AARS [22–24].

Randomized evidence specific to pediatric AARS remains limited, and objective markers of muscle recovery are rarely incorporated into clinical studies in this field. This study was designed to address both gaps by combining a randomized comparison of two conservative treatment strategies with ultrasound-based outcome assessment [23,25,26].

The primary objective is to determine whether joint mobilization combined with cervical resistance training is superior to joint mobilization alone for reducing affected-side sternocleidomastoid muscle stiffness at week 4. Secondary objectives are to compare the effects of the two interventions on pain, cervical disability, cervical rotation range of motion, additional SWE parameters in the sternocleidomastoid and upper trapezius muscles, recurrence-related outcomes during follow-up, and the occurrence of intervention-related adverse events.

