### Blinding

Because the two interventions differ clearly in content and delivery, blinding of participants and treating therapists is not feasible. To minimize bias, outcome assessors, ultrasound examiners, and statisticians will remain unaware of treatment allocation, and participants and their guardians will be reminded not to disclose group assignment during outcome assessments.

Unblinding of blinded study personnel will be permitted only when knowledge of treatment allocation is necessary for participant safety or urgent clinical management. Any unblinding will be decided by the principal investigator, documented with the reason, and restricted to the minimum personnel necessary. Data analysts will remain blinded until the main analysis is completed whenever possible.

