#### Intervention group: Joint mobilization plus cervical resistance training.

Participants in the intervention group will receive the same joint mobilization procedure as the control group, followed by structured cervical resistance training designed to improve muscle activation, neuromuscular control, and dynamic cervical stability.

Before resistance training, selective activation of the deep cervical flexor muscles will be performed in a supine crook-lying position with gentle cranio-cervical flexion while neutral cervical alignment is maintained. Light tactile cueing may be used to reduce substitution by superficial cervical muscles. This preparatory part will usually include 2–3 sets of 5 repetitions.

Manual resistance exercise will then be performed in four directions: flexion, extension, rotation, and lateral flexion [15,16,18]. All exercises will be isometric, with the cervical spine kept in a neutral position. Each contraction will be held for 5–8 s, followed by 5–10 s of rest. Participants will complete 8–10 repetitions per set and 2–3 sets in each direction. Resistance will be applied manually by the therapist. It will be progressed according to tolerance, symptom response, and movement control by adjusting therapist-applied resistance, contraction duration, or repetition number. Maximal effort testing will not be used. Training will be stopped or modified if pain rises clearly, compensatory movement becomes obvious, or the child cannot maintain the required position. Each treatment session will last about 15–20 min.

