#### Safety monitoring.

All adverse events will be recorded during the intervention and follow-up periods. Adverse events will be assessed systematically at each treatment session and follow-up contact and will be classified by severity and relatedness to the intervention. Expected mild events may include temporary neck soreness, brief discomfort during exercise, or transient dizziness. The allocated intervention will be stopped if a participant develops intolerable symptoms, marked worsening of neurological signs, a serious adverse event or another condition requiring alternative medical management. Serious adverse events will be reported promptly to the ethics committee in accordance with local requirements.

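### The secondary safety objective compares the arms only on intervention-related adverse events, which leaves it open to differential attribution; all recorded events should be compared instead

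*Protocol article*

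**What the plan says.** The objectives paragraph that closes the Introduction of the protocol article sets out what the two interventions will be compared on. Its last items are "recurrence-related outcomes during follow-up, and the occurrence of intervention-related adverse events". This is the only place where the article states a between-arm comparison for safety.

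The Safety monitoring section is wider: "All adverse events will be recorded during the intervention and follow-up periods". Events are sought at every treatment session and follow-up contact, and they "will be classified by severity and relatedness to the intervention". The section does not say who makes that classification. It gives examples of expected events: "Expected mild events may include temporary neck soreness, brief discomfort during exercise, or transient dizziness".

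Under Blinding, "blinding of participants and treating therapists is not feasible", while "outcome assessors, ultrasound examiners, and statisticians will remain unaware of treatment allocation". The judgement of relatedness is not assigned to any of these roles. Trial oversight states that there is no endpoint adjudication committee, and a separate section states that there is no data monitoring committee. The Missing data section says that adverse events are not imputed and are summarised as observed. It names no between-arm test and applies no relatedness filter.

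**The concern.** Whether a child had an adverse event can be compared between arms as randomised. Whether that event was caused by the intervention is a further judgement, made after allocation, and knowledge of the treatment can influence it. Restricting the comparison to events that pass this judgement makes the result depend on two quantities: the event rate and the share of events called related. Only the first is the safety effect of interest.

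The setting leaves room for the second to differ. Both arms receive mobilization; in the intervention arm it is "followed by structured cervical resistance training designed to improve muscle activation, neuromuscular control, and dynamic cervical stability". Neck soreness could follow mobilization, exercise or the disease itself, so attributing it is a real judgement. A therapist who has just supervised resistance work may call it related more readily than one who has only mobilised the neck, or less readily if soreness is regarded as normal after exercise. Either direction is plausible.

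At stake is the one comparative statement about safety that the trial sets out to make, in children, for an added exercise component.

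**Working it through.** **1. What is compared and what is collected.** The objective covers related events. Safety monitoring covers all events, with relatedness as a label. The unfiltered comparison can therefore be made from data already planned.

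**2. The plan's own figure.** The article states no figure for adverse events. The only figure used here is the group size, which reproduces by the normal approximation: 2 × (1.960 + 0.842)² × 9.0² / 6.5² = 30.1, rounded up to 31 per group; 31 / 0.90 = 34.4, rounded up to 35. It serves only as the denominator below.

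**3. How a filter can distort.** Let p be the true proportion of children with an event, equal in both arms, and let q be the share of those events called related (q_I in the intervention arm, q_C in control). Then:

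- rate compared = p × q
- spurious difference = p × (q_I − q_C)
- spurious ratio = q_I / q_C

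Both p and q are assumptions, because the documents give neither. The last column is the exact probability that Fisher's test gives P < 0.05 with 35 per arm. The plan names no test for adverse events, so this column is only a gauge.

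| p | q_I / q_C | Related rates | Difference | Ratio | P < 0.05 |
|---|---|---|---|---|---|
| 20% | 80% / 80% | 16% v 16% | 0 | 1.00 | 2.3% |
| 20% | 80% / 60% | 16% v 12% | 4 points | 1.33 | 3.5% |
| 20% | 90% / 40% | 18% v 8% | 10 points | 2.25 | 13.3% |
| 40% | 80% / 80% | 32% v 32% | 0 | 1.00 | 2.9% |
| 40% | 80% / 60% | 32% v 24% | 8 points | 1.33 | 7.2% |
| 40% | 90% / 40% | 36% v 16% | 20 points | 2.25 | 38.1% |

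With all events compared instead, the expected difference is 0 in every row, and Fisher's test is significant in 2.5% (p = 20%) to 2.8% (p = 40%) of trials.

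**4. The opposite direction.** Swapping 80% and 60% turns the ratio of 1.33 into 60/80 = 0.75. A filter can also hide a real difference: with true rates of 30% and 20% and attribution of 60% and 90%, the related rates are 0.30 × 0.60 = 18% and 0.20 × 0.90 = 18%.

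**5. What this shows.** The distortion is proportional to q_I − q_C. It is zero when attribution is equal, and moderate unequal attribution (80% v 60%) seldom gives a significant result at this sample size. Nothing in the article fixes the value or the sign of q_I − q_C.

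**The case against.** **The person who classifies relatedness may be blinded.** A reader might infer that relatedness is decided by someone who knows the arm, and that the comparison is therefore biased. The article does not say so. It does not name who decides, and events are sought at follow-up contacts as well as at sessions run by unblinded therapists. Knowledge of the arm is likely for events raised at sessions, but that is an inference. This objection stands: the most that can be said is that the comparison is open to bias.

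**The Methods do not filter.** All events are recorded, and the summary mentioned under Missing data is not restricted by relatedness. It would be wrong to read the plan as discarding unrelated events. This also stands, but it makes the correction easy and does not change the objective, which still names only related events.

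**Exercise discomfort is not an artefact.** One of the three expected events can occur only where exercise is given, and a reader might take that as evidence of biased attribution. It is not. Discomfort while exercising is a genuine effect of the added component, the list is open and not specific to an arm, and an all-event comparison would carry the same asymmetry.

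**Comparing all events is not bias-free either.** Unblinded children report events to unblinded therapists, and the Discussion acknowledges more therapist contact in the intervention arm. Ascertainment could still differ. That is correct; the change removes the attribution step only.

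**This is detail for the analysis plan.** How events are tabulated can be left to that document. What the objective compares is fixed here, and an analysis plan would be expected to follow it.

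**Conclusion.** The point holds as a minor one. The secondary safety objective is narrower than the safety data the trial collects, and the narrowing rests on a causal judgement that is not stated to be blind or adjudicated, in a trial where therapists and families know the allocation. The stated comparison is therefore open to differential attribution.

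The size and direction cannot be derived from the documents. Under the assumed inputs (equal true rates of 20% to 40%, attribution from 80% v 60% to 90% v 40%), the spurious difference runs from 4 to 20 percentage points. It is zero if the same share of events is called related in both arms. The documents support neither the statement that the comparison is biased nor the statement that it favours a particular arm.

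The objective is secondary, carries no formal test and was not used to size the trial. The primary analysis is unaffected.

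**What to change.** In the objectives paragraph of the Introduction, replace the comparison of intervention-related adverse events with a comparison of all adverse events regardless of relatedness, by assigned arm. Express it as the number of children with at least one event in each arm, with the between-arm difference and its confidence interval. Keep intervention-related events as a descriptive secondary summary.

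The cost is a change of wording in one objective and one table from data already planned; no extra visits, measurements or participants are needed. Two downsides remain. Unrelated childhood illness will add background events to both arms and make the comparison noisier. Unblinded reporting of events also remains and should be acknowledged as a limitation.

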## Methods

### Study design

This study is a single-center, randomized, controlled, two-arm, parallel-group superiority trial. Outcome assessors, ultrasound evaluators, and statisticians will remain blinded to group allocation. Because the two interventions differ clearly in content and delivery, participants and treating therapists cannot be blinded. Fig 1 shows the schedule of enrollment, interventions, and assessments, and Fig 2 shows the study flow.

**Fig 1 pone.0359198.g001:**
[figure not shown]
Schedule of enrollment, interventions, and assessments. The figure presents the planned time points for enrollment, allocation, treatment sessions, outcome assessments, and follow-up visits.

**Fig 2 pone.0359198.g002:**
[figure not shown]
Study flow diagram. The figure summarizes screening, randomization, intervention delivery, outcome assessment, follow-up, and analysis procedures for the randomized controlled trial.

### Study setting

The trial will take place in the Department of Tuina, Hangzhou Hospital of Traditional Chinese Medicine in Hangzhou, China. Potential participants will be recruited consecutively through outpatient screening, inpatient consultation, and referral from related departments at the study site until the target sample size is reached. Investigators will regularly review screening logs and recruitment progress to support timely enrollment.

### Participants

#### Diagnostic criteria.

Eligible participants must meet both clinical and imaging criteria for AARS. Clinical diagnosis will be based on painful torticollis, abnormal head posture, and limited cervical rotation. Imaging confirmation will be based on cervical radiography and/or computed tomography demonstrating atlantoaxial rotational asymmetry or rotatory subluxation, as interpreted by the treating clinical team according to routine institutional practice. When necessary, additional imaging may be used to support diagnosis and exclude alternative cervical pathology [27,28].

#### Inclusion criteria.

(1) age 2–18 years;(2) clinically and radiologically confirmed AARS;(3) stable general condition, ability to follow simple instructions, and ability to complete the intervention and outcome assessments;(4) written informed consent from a legal guardian.

#### Exclusion criteria.

(1) congenital cervical malformation, cervical spine fracture, spinal tumor, spinal infection, inflammatory cervical instability that needs disease-specific treatment, or severe neurological disease;(2) previous cervical spine surgery;(3) severe traumatic AARS, progressive neurological deficit, or another condition that requires urgent reduction or surgical treatment;(4) severe cardiopulmonary disease or another systemic disorder that prevents participation;(5) inability to cooperate with ultrasound examination or functional assessment;(6) other structured cervical rehabilitation, manual therapy, traction, acupuncture, or invasive cervical treatment within 2 weeks before enrollment; or(7) participation in another clinical trial within the previous 3 months.

#### Withdrawal criteria.

Participants may be withdrawn if a legal guardian withdraws consent, if the child cannot continue the intervention or key outcome assessments, if a serious adverse event or clear clinical deterioration requires another treatment, or if a major protocol violation makes continued participation inappropriate. The reason and timing of withdrawal will be recorded. When possible, data collected before withdrawal will be kept for intention-to-treat analyses in line with consent and local regulations.

### Ethical approval and informed consent

This study was approved by the Ethics Committee of Hangzhou Hospital of Traditional Chinese Medicine (Approval No. 2024KLL088). The trial will be conducted in accordance with local legislation, institutional requirements, and the principles of the Declaration of Helsinki. Written informed consent will be obtained from legal guardians by a trained investigator before any study-specific procedures. Assent will be sought from children when appropriate using age-appropriate explanations. Important protocol modifications will be submitted to the ethics committee for approval before implementation unless an immediate change is required for participant safety.

Relevant protocol amendments will also be updated in the trial registry and communicated to investigators, participants, and legal guardians as appropriate. Participants who experience harm or clinical deterioration during the trial will receive appropriate medical evaluation and treatment according to usual clinical practice. No special ancillary care or financial compensation beyond standard institutional and legal arrangements is planned. Study findings will be disseminated through peer-reviewed publications, academic conferences, and trial registry updates where appropriate. A plain language summary will be available to participating children and their legal guardians on request. No biological specimens will be collected, and no ancillary studies requiring additional consent are planned.

